## Abstract

Chronic obstructive pulmonary disease (COPD) is a respiratory disease characterized by the presence of chronic airflow obstruction. Previous studies have evaluated the effect of acupuncture treatment (AT) in patients with COPD. Nevertheless, these studies show a great deal of heterogeneity in treatment protocols, having sample sizes that are too small to estimate and clarify effect size and heterogeneity in patients’ baseline. The aim of this study is to evaluate the effectiveness of acupuncture on quality of life, functional performance, dyspnea, and pulmonary function in patients with COPD. As such, patients will go through the following three phases: Phase I–pretreatment: period of subject selection and inclusion in the protocol, with an interview and performance of exams and tests as follows: Mini-Cog, dual-energy X-ray absorptiometry, spirometry, the Patient-Generated Index, Saint George’s Respiratory Questionnaire, the six-minute walk test, the London Chest Activity of Daily Living, and the COPD Assessment Test. Phase II–8 weeks of treatment, with AT 3 times a week, with two parallel groups: Group I–with 50 subjects–AT according to the recommended technical standards; Group II–with 50 subjects–Control, without acupuncture. Phase III–Continuation of AT for 8 weeks, maintaining the subjects in the previously allocated groups and following the same methodology.

## 1. Introduction

Chronic obstructive pulmonary disease (COPD) is a preventable and treatable respiratory disease characterized by the presence of chronic airflow obstruction that is not fully reversible [1] and by the presence of systemic oxidative stress and inflammation biomarkers [2,3]. Studies on the prevalence of COPD suggest that around a quarter (¼) of adults aged 40 years and older have moderate airflow obstruction [4].

Although COPD compromises the lungs, it also has significant systemic consequences [1,4,5,6]. COPD patients often adopt a sedentary lifestyle that can precipitate the onset of muscle deconditioning through inactivity and a cycle of clinical deterioration [1,7,8,9], negatively impacting the quality of life of patients with COPD [1,10]. Thus, although these patients maintain activities of daily living (ADL) related to self-care, mobility, food, and personal hygiene, their ADLs are considered to be of lesser intensity when compared to healthy individuals [11]. The same is true for physical activity as COPD patients often maintain lower levels of physical activity, according to international guidelines for maintaining physical health [7,8].

The concept of quality of life (QoL) refers to objective and, to a greater extent, subjective indicators of happiness and satisfaction [12]. According to the World Health Organization, QoL is defined as “an individual’s perception of their position in life in the context of the culture and value system in which they live, and in relation to their goals, expectations, standards, and concerns” [13]. In this sense, the administration of questionnaires to assess the HRQoL of patients with COPD has been widely used, generating reliable, valid, and reproducible evidence [14,15].

The complementary role of acupuncture in alleviating the symptoms of various diseases has become increasingly relevant [16]. It is currently accepted that the stimulation of acupuncture points causes the release of neurotransmitters in the central nervous system, in addition to other substances responsible for the responses promoting analgesia, restoration of organic functions, and immune modulation. The World Health Organization recommends acupuncture to its member states, having produced several publications on its efficacy and safety, training of professionals, research methods, and evaluation of the therapeutic results of complementary and traditional medicines [17,18]. In addition, the consensus of the National Institutes of Health of the United States endorsed the indication of acupuncture, alone or as an adjunct, in several chronic conditions including COPD [19]. Additionally, a portion of COPD patients do not respond significantly to pulmonary rehabilitation, and therefore require alternative forms of intervention [20].

Previous studies have evaluated the effect of acupuncture treatment (AT) on COPD patients [21,22], but recent systematic reviews demonstrate great heterogeneity in treatment protocols, including different types and numbers of points of acupuncture, treatment regimens, treatment durations, inappropriate sample size to estimate and clarify effect size, and heterogeneity in the main outcomes of patients evaluated at baseline and in treatments received, demonstrating low methodological quality [23,24]. In addition, there are also studies that evaluate the additive effect [21] and studies that compare AT with certain other interventions [25], leaving a gap regarding the isolated effect of AT. This study hypothesizes that AT will result in an improvement in the quality of life (primary outcome) of patients with COPD, in addition to an improvement in functional performance and pulmonary function, promoting a reduction in the impact of the disease on the lives of such patients.

## 2. Materials and Methods

### 2.1. Design

The study will be a two-arm, parallel-group, prospective, computer-randomized, controlled, evaluator-blind design lasting for 16 weeks (two eight-week intervention periods). The study was registered on the www.ensaiosclinicos.gov.br (accessed on 23 May 2022) (REBEC) website. The protocol has been developed according to the SPIRIT guidelines [26] and described according to the CONSORT statements [27]. The acupuncture protocol will follow the recommendations of the Standards for Reporting Interventions in Clinical Trials of Acupuncture (STRICTA), a formal extension of CONSORT. STRICTA was designed to improve the integrity and transparency of reporting interventions in clinical trials of acupuncture so that such trials can be more accurately interpreted and easily replicated [28]. Furthermore, the intervention will be reported according to the Model for Intervention Description and Replication (TIDieR) checklist and guide [29].

### 2.2. Patients

Patients with a clinical diagnosis of COPD who meet the inclusion criteria will be recruited from the waiting list of the Federal University of the Jequitinhonha and Mucuri Valleys (UFVJM) Physiotherapy school clinic, as well as in doctors’ offices and hospitals and through pamphlets and advertisements on local radio.

Patients will be aware that they will be randomized into one of two groups. Group I will receive AT and Group II will be without AT–we chose a control group without any intervention in order to analyze the isolated effect of AT. At the end of the project, if the results are favorable, patients in the control group will be offered the possibility of receiving AT.

The sample size was estimated using the GPower^®^ program (Franz Faul, Universitat Kiel, Kiel, Germany), version 3.1.9.2. For this, a priori analysis was used, considering the t-test for comparisons between groups, for the quality-of-life variable evaluated by the Saint George Respiratory Questionnaire (SGRQ)-Total score [22]. Thus, considering an effect size of 0.59 [22], power of 0.80%, and alpha error of 5%, the sample size was estimated at 50 patients for each group, totaling 100 patients. These calculations assumed a 20% loss in the worst-case scenario.

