### 2.8. Analyses

Statistical analysis will be performed following the intention-to-treat principle. Data will be analyzed using the SPSS Statistics statistical package (v.22.0; IBM Corp, Armonk, NY, USA). The normality of the data will be verified using the Kolmogorov-Smirnov test and the homoscedasticity of the data through the Levene test. The parametric data will be expressed as mean and standard deviation. In the case of nonparametric data, the median and its upper and lower limits will be expressed. The data will be analyzed using generalized linear mixed-effects models for repeated measures with post hoc Bonferroni analysis for correction. For all tests, an alpha of 5% will be adopted. Effect sizes will be interpreted based on their minimal clinically important differences (MCIDs).

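### The 50 per group does not follow from its stated inputs: if the test is two-sided, which the protocol never says, power after the assumed 20% loss is about 74%, not 80%

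*Protocol article*

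**What the plan says.** The calculation is in section 2.2 (Patients) of the protocol article. It was run as an a priori analysis in G*Power, "considering the t-test for comparisons between groups, for the quality-of-life variable evaluated by the Saint George Respiratory Questionnaire (SGRQ)-Total score". The inputs and result are given as "effect size of 0.59 [22], power of 0.80%, and alpha error of 5%, the sample size was estimated at 50 patients for each group", 100 in total. The paragraph closes with "These calculations assumed a 20% loss in the worst-case scenario", so the 50 is presented as already covering attrition.

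Section 2.8 (Analyses) adds only "For all tests, an alpha of 5% will be adopted". Neither section says whether that 5% is one- or two-sided. The printed power of 0.80% is an evident slip for 80%.

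**The concern.** Apart from sidedness, section 2.2 gives every input of a standard calculation, so a reader can repeat it. A reader who does so with the usual two-sided test gets a requirement well above 50 once a 20% loss is included. The stated figure looks closer to the number needed with almost no loss.

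What is at stake is how a null result on the primary outcome would be read. The paragraph tells readers that the trial keeps 80% power in its worst case. If the true figure there is 74%, the chance of missing an effect of 0.59 is about 26% instead of 20%. The Introduction criticises earlier acupuncture trials for inadequate sample size, so the trial's own sizing statement should stand up to a check.

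**Working it through.** **Inputs.** From section 2.2: standardised difference d = 0.59, power 80% (reading 0.80% as a slip), alpha 5%, equal groups, loss 20%, two-sample t-test. Sidedness is not stated, so both versions are shown.

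**Formula.** With n evaluable per group, the test has 2n − 2 degrees of freedom and noncentrality d × √(n/2). Power is the probability that a noncentral t variable with that noncentrality exceeds the critical t value (in either direction if two-sided). The number to randomise is n / (1 − 0.20).

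**Attempt to reproduce 50.**

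| Reading | Evaluable per group for 80% | Randomised, n/0.8 | Variant, n × 1.2 |
|---|---|---|---|
| Two-sided 5% | 47 (46 gives 79.9%, 47 gives 80.8%) | 58.75, so 59 | 56.4, so 57 |
| One-sided 5% | 37 | 46.25, so 47 | 44.4, so 45 |

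The normal approximation is close. Two-sided, 2 × (1.960 + 0.842)² / 0.59² = 45.1, so 46. One-sided, 2 × (1.645 + 0.842)² / 0.59² = 35.5, so 36. After division by 0.8 these become 58 and 45. None of these figures is 50.

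**Power that 50 per group delivers, two-sided 5%, d = 0.59.**

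| Loss | Evaluable per group | Noncentrality | Power |
|---|---|---|---|
| 0% | 50 | 0.59 × √25 = 2.95 | 83.2% |
| 6% | 47 | 0.59 × √23.5 = 2.86 | 80.8% |
| 10% | 45 | 0.59 × √22.5 = 2.80 | 79.0% |
| 15% | 42.5 | 0.59 × √21.25 = 2.72 | 76.7% |
| 20% | 50 × 0.8 = 40 | 0.59 × √20 = 2.64 | 74.1% |

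The 80% mark is therefore lost once attrition passes about 6%, since (50 − 47)/50 = 6%. With 40 evaluable per group, 80% power requires d of about 0.63. Against the two-sided requirement, the shortfall is 59 − 50 = 9 per group, or 18 in total.

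**Same check, one-sided 5%.** Forty evaluable per group give 83.4% power. The requirement of 47 randomised is below 50, so on this reading the group size is adequate, though still not the number the inputs produce.

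**The case against.** The strongest reply is that the protocol never states a two-sided test. The hypothesis in the Introduction is directional: it expects an improvement. With a one-sided 5% test, 50 exceeds the 47 needed and the claim of at least 80% power after loss is true. This part of the reply stands: a reader might infer that the stated inputs by themselves require 59 per group, but they do so only once two-sidedness is added as an assumption. What does not stand is the step from a directional hypothesis to a one-sided test. No one-sided test is declared, and section 2.8 plans mixed models with Bonferroni post hoc comparisons at a plain 5%, for which two-sided is the ordinary reading.

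A second reply is that 74% applies only to the worst case. The Discussion aims to measure a key outcome in more than 85% of patients. That is fair, but at 15% loss the two-sided power is still about 77%.

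A third reply is that the planned analysis is not this t-test. Section 2.8 and its paragraph on missing data specify repeated-measures mixed models under intention to treat, with imputation for some dropouts, so a patient lost after week 8 still contributes. This also stands. A reader might infer that the trial's actual type II error is 26%, but the document does not support that: it gives no correlation between visits, so the power of the planned model cannot be computed. The 74% describes the test on which the trial was sized.

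**Conclusion.** The concern holds in conditional form. Section 2.2 omits sidedness, and no t-test with its stated power and loss gives 50 per group. On the conventional two-sided reading, the stated inputs need 47 evaluable and 59 randomised per group, and 50 per group falls about six percentage points short of 80% power in the loss scenario it is said to cover. On a one-sided reading there is no shortfall, but the protocol would have to declare that test.

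These figures rest on three assumptions: 0.80% means 80%, 0.59 is the standardised between-group difference used in the t-test, and lost patients contribute nothing to that test. The first is plain from context; the other two follow the way section 2.2 presents the calculation. The error lies in the sizing statement. It does not affect the type I error or the treatment estimate.

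**What to change.** Keep 100 patients and rewrite the justification in section 2.2:

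- State that the test is two-sided at 5% and correct 0.80% to 80%.
- Replace the claim that the 20% loss is covered with: 50 per group gives 83% power (two-sided 5%, d = 0.59) with complete follow-up and 74% if 20% are lost (40 per group, detectable d about 0.63).
- Add that this is the power of the t-test used for sizing, not of the mixed model in section 2.8.

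If a one-sided test was intended, say so in section 2.2 and make the analysis in section 2.8 match. The power after 20% loss may then be given as about 83%.

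A justification based on a baseline-adjusted analysis might recover power, but should be used only with a declared baseline to follow-up correlation and a declared standard deviation basis for the 0.59. The protocol gives neither.

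The cost is two or three sentences and a less favourable stated power. It needs no extra patients and, on the two-sided reading, no change to the design or analysis.

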### 2.3. Randomization

Randomization will be generated by a website (https://www.randomizer.org/ (accessed on 23 May 2022)) and performed by a researcher not involved in the recruitment, treatment, or evaluation of patients. This investigator will be instructed not to disclose the scheduled intervention to the other investigators until the completion of the study. Since randomization will occur after the initial evaluation, it is characterized as a blind distribution. The sequence will be generated in blocks of four patients in random order. The allocation will be hidden in numerical sequence, in opaque sealed envelopes.

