Our work predicts a score of 8 on the PEDro scale as we plan to specify eligibility criteria, randomly assign patients, and use veiled subject allocation by a researcher designated exclusively for this role during research planning, performed using a computer program; we will have well-defined inclusion and exclusion criteria ensuring similar groups with regard to the most important prognostic indicators at baseline; and there will be blinding of the evaluators who will measure the outcomes. Furthermore, we will aim to ensure patient adherence, ensuring that measurements of at least one key outcome will be obtained in more than 85% of subjects initially distributed among the groups, using weekly telephone calls made to patients in the control group; data will be analyzed by intent to treat; we will describe the results of intergroup statistical comparisons in at least one key result; and we will describe measures of precision as measures of variability for at least one key outcome. We will lose in points that do not apply to studies with acupuncture, i.e., blinding of subjects and blinding of the therapist who will apply the therapy. In addition, we will follow up for a total of 16 weeks by reapplying the tests and questionnaires at 8 weeks, which will enable assessment of the responses in the short and long term, which, according to our previous review, has not yet been undertaken.

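### A single published block size of four, with patients and therapist unblinded, makes up to a third of assignments predictable to anyone who knows the past allocations in order

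*Protocol article*

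**What the plan says.** Section 2.3 (Randomization) of the protocol article states: "The sequence will be generated in blocks of four patients in random order". Four is the only size given. The phrase about random order describes how patients or blocks are arranged; it does not say that the size varies. No stratification factor is mentioned.

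The same section lists the safeguards. The list comes from a website and is handled by a researcher with no part in recruitment, treatment or evaluation, who must not disclose allocations to the other investigators before the study ends. Randomisation follows the initial evaluation. On concealment it says: "The allocation will be hidden in numerical sequence, in opaque sealed envelopes".

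Section 2.1 (Design) describes a "two-arm, parallel-group, prospective, computer-randomized, controlled, evaluator-blind design". The Discussion accepts that the trial forgoes two quality-scale points, for "blinding of subjects and blinding of the therapist who will apply the therapy". Section 2.2 (Patients) explains the comparator: "we chose a control group without any intervention in order to analyze the isolated effect of AT". The same section gives the size: "the sample size was estimated at 50 patients for each group, totaling 100 patients".

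**The concern.** Sealed envelopes hide the content of the next envelope. They do not hide what can be worked out from a known block size and a known run of earlier allocations. Here the earlier allocations are easy to observe: one arm attends for needling three times a week and the other does not, and the Discussion adds weekly telephone calls to control patients, so whoever makes those calls also knows the arm. The block size is in a published article.

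Someone who can predict the next assignment could, knowingly or not, choose whom to call next or when to call them. There is room for this. Section 2.2 recruits partly from a clinic waiting list, and some criteria in section 2.4 depend on timing or judgement, such as a recent stable period and the ability to perform the assessments. Ordering the evaluation before randomisation does not remove the opportunity, because the prediction can be made before deciding whom to bring to evaluation. If patients expected to do well went preferentially to one arm, the comparison of quality of life would be biased from the start.

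**Working it through.** The article states no predictability figure, so there is none to reproduce. The check is an exact enumeration.

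Inputs:
- Block size 4, one size only (section 2.3).
- Two arms (section 2.1), 50 per arm, 100 in total (section 2.2). Two places per arm in each block is implied by the equal arms; it is not stated.
- Number of blocks: 100 / 4 = 25.
- Assumed: one unstratified list, and an observer who knows the block size and every earlier allocation in enrolment order.

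**Fixed blocks of four.** Two places per arm give 4! / (2! × 2!) = 6 equally likely arrangements. An assignment is certain when one arm has used both its places. The best guess is the arm with more places left, or a coin toss when they are equal.

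| Position in block | Probability that it is certain | Probability that the best guess is right |
|---|---|---|
| 1 | 0 | 1/2 |
| 2 | 0 | 2/3 |
| 3 | 2/6 = 1/3 | 1/3 × 1 + 2/3 × 1/2 = 2/3 |
| 4 | 1 | 1 |
| Sum | 4/3 | 17/6 |

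- Share certain: (4/3) / 4 = 33.3%.
- Expected number over 25 blocks: 25 × 4/3 = 33.3 of 100 patients, made up of 25 fourth places and about 8.3 third places.
- Best guess right: (17/6) / 4 = 17/24 = 70.8%, against 50% without information.

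**Varying block sizes.** This was simulated with 4,000 trials of 100 patients. The observer knows the set of possible sizes and all past allocations but not the size of the current block, and updates the probabilities after each patient. The sets of sizes are illustrative.

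| Block sizes | Certain | Best guess right |
|---|---|---|
| 4 only, exact | 33.3% | 70.8% |
| 4 only, simulated as a check | 33.4% | 70.8% |
| 2, 4, 6 | 4.1% | 70.1% |
| 4, 6 | 5.5% | 69.2% |
| 4, 6, 8 | 2.3% | 67.9% |

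Varying the size removes nearly all the certainty but little of the guessing advantage.

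**Final imbalance.** With a largest block of 8, an incomplete last block can leave the arms at most 8 / 2 = 4 patients apart. With a fixed size of four, 100 patients fill 25 complete blocks and the arms end equal.

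**The case against.** The strongest reply is that the article never says that the therapist, or anyone else who sees allocations, recruits patients or decides eligibility. The list holder is independent and told not to disclose, the evaluators are blinded, and the Discussion also speaks of blinding the researcher to allocation. Patients come from doctors' offices, hospitals and advertisements as well as the clinic's own list. An evaluator who stays blind to past allocations could predict nothing. This stands: 33% is the expectation for a fully informed observer, hence a ceiling, and not an estimate of what happens in this trial.

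A reader might infer that recruiting staff do know the allocations, or that a third of this trial's patients are in effect not concealed. The documents support neither. A reader might also infer that any resulting bias would be undetectable. That goes too far: SGRQ, PGI, spirometry, walking test, LCADL and CAT are all measured in Phase I, so steering on measured severity could appear as a baseline imbalance and be examined or adjusted for. Steering on unmeasured traits, such as motivation, would escape.

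It is also fair that concealment is only one of several items behind the predicted quality score, that the absence of stratification is read from the silence of a condensed article, and that the remedy leaves most of the best-guess advantage in place.

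The core is untouched. None of the listed safeguards varies the block size or hides who is being treated, and the article describes no separation of unblinded staff from recruitment.

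**Conclusion.** The point holds as a conditional design weakness. It is neither an error of arithmetic nor a contradiction in the plan. With a fixed, published block of four, an observer who knows the past allocations in order can name an expected 33% of assignments with certainty, about 33 of 100, and guesses correctly 71% of the time.

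This rests on two places per arm in each block, a single unstratified list, and knowledge of past allocations reaching someone who influences recruitment or eligibility. The first two follow from, or fit, what the article says. The third is open. The conclusion is therefore a risk of selection bias that has not been shown to occur, and that baseline data would reveal only in part. The change is still worth making because it costs almost nothing and removes nearly all the certainty.

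**What to change.** The independent researcher should generate the list with block sizes that vary at random, for example 4, 6 and 8, and should not disclose the sizes to recruiting or treating staff. If recruitment has begun, apply the new rule to the unused envelopes, starting once the current block of four is complete, and record the date of the change. Section 2.3 already places randomisation after the initial evaluation, so no change to the timing of envelope opening is needed.

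With sizes 4, 6 and 8, certain assignments fall from 33.3% to about 2.3%; the best-guess rate falls only from 70.8% to about 67.9%, and the protocol should not claim more than that. The cost is a new list and new envelopes, no effect on patients, and a possible final difference of up to four patients between the arms.
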